## POST-OPERATIVE EVALUATION

## GOLD WEIGHT IMPLANT

[illegible]

## APPENDIX 5

## POST-OPERATIVE EVALUATION

## MODIFIED TARSORRHAPHY

[illegible]

## APPENDIX 6

### OCULAR SURFACE DISEASE INDEX

| Have you experienced any of the following during the last week?                                          | All of the time | Most of the time | Half of the time | Some of the time | None of the time |
|----------------------------------------------------------------------------------------------------------|-----------------|------------------|------------------|------------------|------------------|
| A. Eyes that are sensitive to light?                                                                     | 4               | 3                | 2                | 1                | 0                |
| B. Eyes that feel gritty?                                                                                | 4               | 3                | 2                | 1                | 0                |
| C. Painful or sore eyes?                                                                                 | 4               | 3                | 2                | 1                | 0                |
| D. Blurred vision?                                                                                       | 4               | 3                | 2                | 1                | 0                |
| E. Poor vision?                                                                                          | 4               | 3                | 2                | 1                | 0                |
| Have problems with your eyes limited you in performing any of the following during the last week? |                 |                  |                  |                  |                  |
| F. Reading?                                                                                              | 4               | 3                | 2                | 1                | 0                |
| G. Driving at night?                                                                                     | 4               | 3                | 2                | 1                | 0                |
| H. Working with a computer or bank machine (ATM)?                                                        | 4               | 3                | 2                | 1                | 0                |
| I. Watching TV?                                                                                          | 4               | 3                | 2                | 1                | 0                |
| Have your eyes felt uncomfortable in any of the following situations during the last week?        |                 |                  |                  |                  |                  |
| J. Windy conditions?                                                                                     | 4               | 3                | 2                | 1                | 0                |
| K. Places or areas with low humidity (very dry)?                                                         | 4               | 3                | 2                | 1                | 0                |
| L. Areas that are air conditioned?                                                                       | 4               | 3                | 2                | 1                | 0                |

OSDI score assessment : Normal: 0 – 12; Mild dry eye: 13 – 22; *Moderate dry eye*: 23 – 32; *Severe dry eye*: 33 – 100

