##### **2.1. Ocular Surface Disease Index (OSDI) Questionnaire**

Subjective symptoms of dry eyes are assessed using OSDI questionnaire that consists of 12 questions regarding dry eyes symptoms. Each question answered with 0-4 Likert scale (0: never, 1: seldom, 2: sometimes, 3: often, 4: always). Final score is calculated with:  $(\text{total score} \times 100) / (\text{total questions answered} \times 4)$ . Final score then categorized into: normal (0-12), mild dry eye (13-22), moderate dry eye (23-32), or severe dry eye (33-100).

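### The OSDI score divides by the questions answered, but the Appendix 6 form offers no way to mark an item as not applicable, so the score can be understated and can shift between visits

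*Protocol*

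**What the plan says.** The protocol, section 2.d Outcomes, 2.1, describes an "OSDI questionnaire that consists of 12 questions regarding dry eyes symptoms". It gives the answer scale as "Each question answered with 0-4 Likert scale (0: never, 1: seldom, 2: sometimes, 3: often, 4: always". The score is the total times 100, divided by four times the "total questions answered". The result is then banded: "Final score then categorized into: normal (0-12), mild dry eye (13-22), moderate dry eye (23-32), or severe dry eye (33-100".

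Appendix 6 prints the form with five answer columns, "All of the time | Most of the time | Half of the time | Some of the time | None of the time", scored 4 to 0. Items F to I (reading, night driving, computer or ATM, television) come under "Have problems with your eyes limited you in performing any of the following during the last week". Items J to L ask about discomfort in wind, low humidity and air conditioning. The form repeats the bands in whole numbers, beginning "OSDI score assessment : Normal: 0 – 12; Mild dry eye: 13 – 22".

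Neither place has a not-applicable answer, an instruction to leave an item blank, or a rounding rule. Neither place says that an item that does not apply scores 0.

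**The concern.** The formula and the form do not fit together. A denominator that counts answered items only has a purpose if some items may be omitted, yet the form invites one of five scored answers to each item. Asked whether eye problems limited night driving, someone who does not drive can truthfully choose the zero column. That answer says nothing about symptoms, but it is averaged in as if it recorded the absence of a limitation.

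Two things are at stake. A patient who always marks 0 for such items has the score, and any change in it, shrunk by a fixed factor. A patient who marks 0 at one visit and leaves the item blank at another shows a change with no change in symptoms. OSDI is the only subjective measure among the listed effectivity outcomes. It is repeated at 1 day, 7 days, 1 month, 3 months and 1 year, with a planned minimum of 12 eyes per group. Once recorded, a zero that means the item does not apply cannot be told from a zero that means no limitation, so later analysis cannot repair it.

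**Working it through.** **Inputs.** From section 2.1: 12 items scored 0 to 4, score = T × 100 / (4k) with T the total and k the items answered, and bands 0-12, 13-22, 23-32, 33-100. From Appendix 6: five answer columns and the same bands. Assumption: the number m of items that do not apply to a patient. The protocol gives no figure, so m = 1 to 4 is shown.

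**The plan's own range.** With k = 12 the maximum is 48 × 100 / 48 = 100, which reproduces the stated 0-100. On a complete form scores move in steps of 100/48 = 2.083.

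**Inapplicable items marked 0 or omitted.** With k = 12 − m items that apply:
- omitted: T × 100 / (4k)
- marked 0: T × 100 / 48
- ratio of the second to the first: k/12

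The last column counts the attainable totals whose category is lower when 0 is marked, with scores rounded half-up to whole numbers before banding.

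| m | k | ratio | totals that change category |
|---|---|---|---|
| 1 | 11 | 11/12 = 92% | 2 of 45 |
| 2 | 10 | 10/12 = 83% | 6 of 41 |
| 3 | 9 | 9/12 = 75% | 7 of 37 |
| 4 | 8 | 8/12 = 67% | 10 of 33 |

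For m = 3 the seven totals are 5, 9, 10, 12, 13, 14 and 15. At T = 15, omission gives 15 × 100 / 36 = 41.7 (severe) and marking 0 gives 15 × 100 / 48 = 31.25 (moderate). Both values lie inside printed bands, so this example does not depend on rounding.

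The count of seven does depend on it. If the bands are instead cut at below 13, below 23 and below 33 without rounding, totals 6 (600/36 = 16.67 against 600/48 = 12.5) and 11 (1100/36 = 30.56 against 1100/48 = 22.92) also move, which makes 9 of 37. These counts treat every total alike and are not proportions of patients.

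**Inconsistency between visits.** Take T = 15 at both visits and one item that does not apply. Marked 0, the score is 15 × 100 / 48 = 31.25. Left blank, it is 15 × 100 / 44 = 34.09. The score moves by 34.09 − 31.25 = 2.84 points and from moderate to severe with identical symptoms. With three such items the shift is 41.67 − 31.25 = 10.42 points.

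**Band gaps.** On a complete form, 2 of 49 attainable scores fall between bands: T = 6 gives 12.5 and T = 11 gives 22.92. With 10 items answered, 12.5, 22.5 and 32.5 do. Rounding to whole numbers classifies every attainable score, but a rule for ties at .5 is still needed.

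**The case against.** The strongest reply is that no zero is forced. Nothing in the protocol requires every item to be ticked, and a blank is handled correctly by the formula in section 2.1. This stands, and it makes the effect conditional. It does not remove the point, because the form never tells the patient or the examiner that a blank is allowed, and the zero column is the obvious choice.

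Second, the number of inapplicable items is not known. The background describes leprosy and its eye complications in the literature, with elderly patients, disability and limited means, but says nothing about driving, ATM use or air conditioning among trial patients. This also stands: the percentages are a range under assumption.

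Third, both randomised arms use the same form, and the planned methods (t-test, Mann-Whitney, Wilcoxon, repeated-measures model) suit the numeric score, with no analysis tied to the categories. The sample size rests on a 1 mm difference, not on OSDI. A reader might infer a biased comparison between the arms, but the document shows no reason why inapplicable items should be commoner in one arm.

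Fourth, rounding and missing-item rules may sit in a statistical analysis plan that is not shown. This holds for the bands but not for the answer box, which belongs to the form. Finally, a column lost when the PDF was read cannot be fully excluded, although the five-column table looks intact.

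**Conclusion.** The point holds in a limited form. The score can be understated, by a factor of 10/12, 9/12 or 8/12 for 2, 3 or 4 inapplicable items marked 0, and it can shift between visits if such items are handled inconsistently. This rests on three assumptions: that some items do not apply to some patients, that 0 is then marked, and that the form is as shown.

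A reader might go further and conclude that dry-eye severity is understated in this trial, or is undefined. The protocol supports neither. Understatement follows only where 0 is marked. The band gaps touch the category and never the 0-100 score, and a rounding rule closes them, so they would not merit a point of their own. What remains is a cheap correction to one of several effectivity outcomes, worth making because it is only possible before the data are collected.

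**What to change.** In Appendix 6, add a not-applicable box to items F to L. In section 2.1, state that items so marked are left out of both numerator and denominator, and that a subject's inapplicable items stay the same across visits unless the activity itself changes.

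As a minor accompanying edit, write the bands in both places without gaps (below 13, 13 to below 23, 23 to below 33, 33 and above), or state a rounding rule that settles ties at .5.

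The cost is a revised one-page form and a few lines of protocol text. The small downside is that some scores will rest on fewer items.
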